## Outcomes

### Primary and Secondary Outcomes

The details of items to be measured and the time window of data collection are shown in Table 5. The primary outcome is the improvement in 6-min walk distance (6MWD) (Holland et al., 2014). 6MWD will be measured within 24 h after enrollment and 12 weeks after treatment to evaluate the change in exercise tolerance. Improvement will be calculated using the following formula:

**TABLE 5 T5:** Study schedule.

Study phase time	Baseline period	Intervention period			Follow-up
	Visit 1	Visit 2	Visit 3	Visit 4	Every 4 weeks
	−7 to 0 days	4 weeks	8 weeks	12 weeks	Until 52 weeks
Data collection at baseline					
Informed consent	×				
Inclusion/exclusion criteria	×				
Demographic data	×				
Obtain the central random number	×				
Previous history, medical history, and allergies	×				
Comorbidities and co-medications	×				
Safety evaluation					
Vital signs	×	×	×	×	
Physical examination	×	×	×	×	
Blood routine	×			×	
Urine routine	×			×	
Blood biochemistry	×			×	
Myocardial zymogram and troponin	×			×	
ECG	×			×	
Chest radiograph or CT	×			×	
Urine pregnancy test	×			×	
Efficiency evaluation					
6MWD	×			×	
NT-proBNP	×			×	
NYHA class	×	×	×	×	
MLHFQscore	×	×	×	×	
Echocardiographic parameters	×			×	
Clinical-endpoint events		×	×	×	×
Other work					
Dispense drug	×	×	×		
Recovery and record of study drug		×	×	×	
Metabolomics and proteomics	×			×	
Record AEs		×	×	×	×
Complications due to medications		×	×	×	
Evaluate compliance		×	×	×	×

CT, computed tomography; 6MWD, 6-min walk distance; NYHA, New York Heart Association; MLHFQ, Minnesota Living with Heart Failure Questionnaire; TCM, traditional Chinese medicine; AE, adverse event.

Improvement in exercise tolerance = 6MWD value after treatment − 6MWD value before treatment

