### Sample Size

The formula for calculating the sample size is based on the superior clinical trial sample size estimation (Wan et al., 2017). The sample size is driven by the expected improvement in 6MWD. Referring to clinical studies (Fan and Zhang, 2012; Guo and Li, 2013; Du, 2014; Wu et al., 2015), we assumed that the improvement in 6MWD is 30 m, and the combined standard deviation (SD) is 100 m in the present study. Given a rate of type-I error of *α* = 0.025, a power of 80% (rate of type-II error of *β* = 0.2), and, considering a possible dropout rate of 20%, 470 patients will need to be allocated. For the convenience of randomization, the final sample size was 320 cases in the intervention group and 160 cases in the placebo group, a total of 480 cases.$$n_{1}={\left[\frac{\left({µ}_{\alpha }+{µ}_{\beta }\right)\sigma }{\delta }\right]}^{2}\frac{\left(1+k\right)}{k},\;n_{2}=k\;n_{1}.$$

In this formula, *k* is the ratio between two sample cases, *δ* is the expected improvement in 6MWD, and *σ* is the combined SD.

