### Statistical Analyses

The statistical analysis plan will be specified before data analyses. The statistical analyses will be undertaken *via* Statistical Analysis System v9.4 (or higher version) by the Department of Medical Statistics, Peking University First Hospital. Professional statisticians who are independent of all other processes of our study will carry out analyses. Consistent with the CONSORT statement and ITT principle, and the last observation, carried forward method will be used for missing values. Cases in the per protocol set (PPS) will be those who adhere to the protocol closely without the absence of baseline characteristics. Analyses of primary outcome and curative effect will be carried out using a full-analysis-set approach and PPS approach. The safety analysis set will include all randomized patients who have accomplished at least one study visit. Participating centers will be required to sum-up participant numbers in each center and list participants who have been removed from PPS.

For continuous variables, we will calculate the mean, SD, median, minimum, maximum, and interquartile range. For categorical variables, we will describe various frequencies or percentages. The chi-square test or Fisher's exact test will be used for categorical variables. The Student's *t*-test will be used for continuous variables with a normal distribution. For data that do not have a normal distribution, intragroup or intergroup differences before and after treatment will be analyzed by the Wilcoxon rank-sum test. The proportion of patients with AEs in two groups will be compared using the chi-square test or Fisher's exact test. Because patients who had use of ARNIs before the recruitment may constitute a specific population, we will run sensitivity analyses of the outcomes with patients used ARNIs as basic treatment, and adjusted for the effect of ARNIs. Significance will be assumed at a two-sided *p*-value less than 5%. The relative risk with corresponding 95% confidence interval to compare dichotomous variables will be calculated. Table 6 shows the method of analysis for specific outcomes.

**TABLE 6 T6:** Outcomes and methods of analyses.

Outcome/variable	Hypothesis	Measures	Methods of analyses
Baseline balance test			
		Quantitative outcomes (age, temperature, heart rate, respiratory rate, and blood pressure)	*t*-test/Wilcoxon rank-sum test

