		Qualitative outcomes (sex, marriage, and previous treatment)	Chi-squared test/Fisher’s exact test/rank-sum test
Adherence at post-intervention		Percent and cases of adherence <80% and ≥80%	Chi-squared test/Fisher’s exact test
Concomitant treatments		Percent and cases of concomitant treatments	Chi-squared test/Fisher’s exact test
Primary outcome			
6MWD	Improvement occurred		*t*-test/Wilcoxon rank-sum test
			Covariance analysis
Secondary outcomes			
NT-proBNP	Improvement occurred		*t*-test/Wilcoxon rank-sum test
NYHA classification	Improvement occurred		Wilcoxon rank-sum test
MLHFQ	Improvement occurred	Questionnaire	*t*-test/Wilcoxon rank-sum test
Echocardiographic parameters	Improvement occurred	Left ventricular end-diastolic diameter and LVEF	*t*-test/Wilcoxon rank-sum test
Clinical endpoint events	Improvement occurred	Clinical-endpoint event rate	Log-rank test
Safety outcomes			
AEs, SAE		Percent and cases of AEs and SAEs	Chi-squared test/Fisher’s exact test
Vital signs		Change value relative to baseline	*t*-test/Wilcoxon rank-sum test

6MWD, 6-min walk distance; NT-proBNP: N-terminal pro-B-type natriuretic peptide; NYHA, New York Heart Association; MLHFQ, Minnesota Living with Heart Failure Questionnaire; LVEF: left ventricular ejection fraction; AE, adverse event; SAE: serious adverse events.

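### Within-arm before–after changes in non-normal variables are assigned the Wilcoxon rank-sum test, which ignores the pairing and makes those p-values too large

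*Protocol article*

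**What the plan says.** The Statistical Analyses section of the protocol article gives one rule for normal and one for non-normal continuous data. For normal data: "The Student's *t*-test will be used for continuous variables with a normal distribution". For non-normal data: "intragroup or intergroup differences before and after treatment will be analyzed by the Wilcoxon rank-sum test". The second rule names one test for two different comparisons, within an arm and between arms.

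The Primary and Secondary Outcomes section shows how the data arise: "6MWD will be measured within 24 h after enrollment and 12 weeks after treatment to evaluate the change in exercise tolerance". The outcome is then defined patient by patient: "Improvement in exercise tolerance = 6MWD value after treatment − 6MWD value before treatment". Table 5 schedules NT-proBNP, the Minnesota questionnaire and echocardiography in the same way, at baseline and again at 12 weeks.

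Table 6 lists a t-test or rank-sum test for the continuous outcomes. Neither the text nor the table mentions a signed-rank test or any other paired test.

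**The concern.** The rank-sum test takes its null variance from two independent samples. Before and after values in one arm are two measurements on the same people and will normally be positively correlated. The variance of the before–after difference is then smaller than the test assumes, so the test statistic is too small and the p-value too large.

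Reading the word differences as change scores does not rescue the within-arm half of the sentence. Within one arm the change scores form a single sample, and a two-sample test cannot be applied to it.

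This is not detail left to a later document: a named test is assigned to a named comparison, and the test does not fit it. At stake is the correctness of any within-arm p-value reported for a non-normal variable. NT-proBNP, which is often skewed, is a likely case.

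**Working it through.** **Plan's own figure.** The plan gives no figure for within-arm tests. Its one computed number, 470 patients, matters here only because it leads to the arm sizes. With the inputs of the Sample Size section (30 m, SD 100 m, α = 0.025 taken as one-sided, power 80%, ratio 2:1):

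- placebo arm: (1 + 1/2) × [100 × (1.960 + 0.842) / 30]² = 130.8
- total: 3 × 130.8 = 392.4
- with 20% added: 392.4 × 1.2 = 470.9, which matches 470

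The planned arms of 320 and 160, less 20% dropout, leave 256 and 128 patients with both measurements.

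**Inputs for the check.**

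- From the protocol: two-sided 5% significance, the arm sizes above, and paired measurement at baseline and 12 weeks.
- Assumed, because the documents do not give it: a before–after correlation ρ, varied from 0 to 0.9.
- Assumed for power: a within-arm shift of 0.2 SD.

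**Approximate size.** If before and after values have common variance σ² and correlation ρ, the difference in means has variance 2σ²(1 − ρ)/n, while an independent-samples test assumes 2σ²/n. The same holds approximately for mean ranks. The test statistic then has variance 1 − ρ under the null instead of 1, and the true size is

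2 × [1 − Φ(1.96 / √(1 − ρ))]

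- ρ = 0: 5.0%
- ρ = 0.3: 1.96 / 0.837 = 2.343, giving 1.9%
- ρ = 0.5: 1.96 / 0.707 = 2.772, giving 0.56%
- ρ = 0.7: 1.96 / 0.548 = 3.578, giving 0.03%

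**Simulation with skewed data.** The rule applies only to non-normal data, so the check used lognormal pairs (log-scale SD 0.8, with ρ and the 0.2 SD shift on the log scale) and 3,000 replicates per row. The simulation error on a 5% rate is √(0.05 × 0.95 / 3,000) = 0.4 percentage points.

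| ρ | n | Size, rank-sum | Size, signed-rank | Power, rank-sum | Power, signed-rank |
|---|---|---|---|---|---|
| 0 | 128 | 4.9% | 4.7% | 35% | 33% |
| 0.3 | 128 | 2.2% | 5.5% | 31% | 41% |
| 0.5 | 128 | 0.7% | 5.5% | 29% | 53% |
| 0.7 | 128 | 0.1% | 4.9% | 25% | 75% |
| 0.3 | 256 | 1.9% | 4.8% | 61% | 70% |
| 0.5 | 256 | 0.6% | 4.6% | 64% | 83% |
| 0.7 | 256 | 0.03% | 4.9% | 68% | 97% |

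At ρ of 0.8 and 0.9 the rank-sum test rejected in none of the 3,000 null data sets, at either sample size. The simulated sizes agree with the formula. The signed-rank test stays near 5% throughout.

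**The case against.** The strongest reply is that this does not touch the trial's question. The hypothesis is superiority over placebo, the primary outcome is a change score per patient, and a rank-sum test of change scores between arms is valid. That stands. It also stands that the error is conservative: with positive correlation it creates no false positives. The cost falls on within-arm p-values, which are secondary in a placebo-controlled trial. The wording may be a slip for signed-rank, but nothing in the article corrects it.

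Some stronger readings are tempting, and the documents do not support them.

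- **Table 6 repeats the error.** It does not show this. Its rank-sum entries are correct as between-arm tests, and no row specifies a within-arm test.
- **The Table 6 hypothesis of improvement implies within-arm claims.** The same phrase stands against clinical endpoint events, which are tested by log-rank and are not collected at baseline. It is loose shorthand. The Introduction states the actual hypothesis against placebo.
- **The t-test rule has the same fault.** Not saying whether the t-test is paired is missing detail that a condensed article may leave to the SAP. It is not a wrong statement.
- **The trial may claim an effect because GXST changes significantly and placebo does not.** No such contrast is planned. If both arms shifted by 0.2 SD with ρ = 0.5, its chance would be 0.635 × (1 − 0.285) = 45% with the rank-sum test and 0.831 × (1 − 0.535) = 39% with the signed-rank test. At ρ = 0.7 the figures are 0.678 × (1 − 0.247) = 51% and 0.966 × (1 − 0.753) = 24%. The wrong test makes it more likely here, but the correct test does not remove it, because the arms differ in size.

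**Conclusion.** The point holds for the within-arm half of one sentence. As written, the plan applies an independent-samples test to paired data, and the resulting p-values would be too large. The size of the error depends on an assumed correlation. At ρ = 0 there is no distortion; at 0.3, 0.5 and 0.7 the nominal 5% test runs at about 2%, 0.6% and at most 0.1%. The loss of power also rests on the assumed 0.2 SD shift, the lognormal shape and 128 patients. More patients may be analysed, because the protocol carries the last observation forward. The size results hardly depend on the number of patients.

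A reader might infer that the efficacy result or the sample size is compromised, or that false positive findings will follow. None of these is the case. This is a limited method error that is cheap to correct and should not go forward into the SAP.

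**What to change.** In the Statistical Analyses section, split the sentence on non-normal data in two:

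- Between arms: differences in change from baseline are compared by the Wilcoxon rank-sum test.
- Within an arm: change from baseline is examined by the Wilcoxon signed-rank test, or by the paired t-test if normally distributed, and is reported as descriptive only.

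Table 6 needs no change for this point. The article says that the SAP will be specified before data analyses, so the correction can be made there. It costs wording only: no extra patients, visits or data, and no change to the sample size or the primary analysis.

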### Adverse Events

AEs that occur during the observation period will be monitored, reported to a research assistant, causality with the intervention will be evaluated, and the severity of AEs will be analyzed. SAEs will be reported to the ethics committee within 24 h. The classification and coding of AEs are formulated concerning Common Terminology Criteria for AEs version 4.03.

### Quality Control of the Intervention

To further ensure the quality of this trial, a multicenter trial coordination committee and general director will be set up for the implementation and solution of the problems related to this trial. The leaders of each center and the sponsor are the members of the coordination committee. Before each center recruits subjects, the sponsor will conduct unified preclinical trial training for all staff. Through such training, all staff (operators, investigators, physicians, data collectors, and analyzers) will fully understand the purpose and content of the trial, and standardize the process of data collection and CRF completion. This trial will be inspected by the CFDA, sponsor, and clinical research organization throughout the trial.

### Trial Status

This is an ongoing trial. The first participant was recruited on September 16, 2019. This study is recruiting participants currently.

## Discussion

CHF continues to be a major cause of mortality, initial and recurrent hospitalizations, and suboptimal quality of life (Yao et al., 2020). Despite advances in management and treatment of CHF, many CHF patients continue to suffer from exercise intolerance and dyspnea (Simpson et al., 2015). An increasing volume of evidence demonstrates that the combination of TCM with Western medicine could be an optimal approach for achieving greater treatment efficacy in patients with CHF (Gao et al., 2017; Jia et al., 2020).

GXST is a widely used TCM formulation for the treatment of cardiovascular disease in China. Pharmacology results have shown the effects of GXST in multiple mechanism pathways to treat CHF, such as improving hemorheology (Liang et al., 2012); enhancing mitochondrial capacity, and improving myocardial energy metabolism (Zhang et al., 2015; Zhang et al., 2016); and reversing ventricular remodeling (Zhang et al., 2012; Zhang et al., 2013). However, whether GXST is efficacious in patients with CHF requires confirmation by large-sample, multicenter, randomized controlled clinical trials. Therefore, we designed a multicenter, double-blinded, placebo-controlled clinical trial with the hope of verifying the efficacy and safety of GXST for the treatment of CHF with reduced LVEF. The results could provide a strategy for combining TCM and Western medicine in CHF patients.

We chose the 6MWD test to assess the functional capacity and exercise tolerance in patients with CHF. The 6MWD test is a simple and convenient test that requires no special equipment or advanced training for physicians and is well tolerated by patients. Although the plasma level of NT-proBNP is used widely in the differential diagnosis, risk stratification, and prognostic evaluation of CHF, use of ARNIs can affect the NT-proBNP level significantly (Yancy et al., 2017). Therefore, we chose the plasma level of NT-proBNP as a secondary outcome, and use sensitivity analyses to adjust the effect of ARNI on the outcomes. Furthermore, we have applied metabolomics and proteomics analyses to explore the therapeutic biomarkers of GXST in treating CHF, and to improve CHF therapy by providing an objective basis for precise treatment.

Our trial has three main limitations. First, this trial will be conducted in five provinces of China, and whether similar effects are obtainable in other regions and ethnic groups are unknown. Second, the treatment period will be 12 weeks with 40 weeks of follow-up, which is relatively short. Due to the limited time frame, the potential roles of GXST in reducing overall mortality and major vascular events over the long-term are uncertain, and further data on long-term clinical effect and safety will be needed. Third, GXST used in this trial is designed for the treatment of CHF with blood stasis syndrome, so the findings may not apply to other CHF syndromes.

### Ethics and Dissemination

The Research Ethics Committee of the Second Affiliated Hospital of Zhejiang Chinese Medical University (Hangzhou, China) has approved the study protocol (2019-Y-003-02). All participating centers have received study approval from their local ethics committee. All participants will provide voluntary written informed consent after a full discussion about the potential benefits and risks before participation. This study will be published in scientific journals to target a wide range of groups, and presented at national conferences in the field of CHF. Study results will also be sent to study participants and disseminated to researchers, as well as the general public through courses, presentations, and the Internet, regardless of the magnitude or direction of influence.

## Ethics Statement

The Research Ethics Committee of the Second Affiliated Hospital of Zhejiang Chinese Medical University has approved this study (No. 2019-Y-003-02). The patients/participants provided their written informed consent to participate in this study.

